## Materials and methods

Method

This experimental study will be conducted in the Department of Prosthodontics, Sharad Pawar Dental College and Hospital, Sawangi (M), Wardha, India. The data will be collected in the postgraduate clinic of the Department of Prosthodontics. On the basis of the inclusion and exclusion criteria (Table 1), the patients will be divided randomly into two groups: Group A (n=20) (herbal denture adhesive without essential oil) and Group B (n=20) (herbal denture adhesive with essential oil). A total of 16 closed-ended questions will be asked of patients: eight during denture insertion without using denture adhesives and eight questions seven days after using denture adhesives.

**Table 1 TAB1:** Inclusion and exclusion criteria

Inclusion Criteria	Exclusion Criteria
Patients who are first-time denture wearers	Patients with tooth-supported overdentures
Patients who are old complete denture wearers	Patients with implant-supported overdentures
Patients who are willing to participate in the study	Patients with a single complete denture

The denture adhesive will be fabricated by utilizing carboxymethylcellulose with flavor, mineral oil, petroleum, silica particles, and mesoporous nanoparticles of the selected essential oil (cinnamon oil) with antimicrobial action incorporated into a gel for prolonged release, giving better effectiveness. In order to gather information about denture fitting, removal, chewing, retention, and phonetics, a standard questionnaire form will be given to each patient. Following the patient's answer to Questionnaire 1 (Table 2), a clinical examination and application of denture adhesive demonstration will take place, adhering to the guidelines provided by the manufacturer. The patients will be provided with an explanation of the cleaning routine and the administration of denture adhesive for the next seven days. The patients will be contacted back a week later to complete an additional questionnaire (Table 3) in which they will be asked to rate the denture's strength, biocompatibility, convenience, and masticatory abilities using the glue that was provided.

**Table 2 TAB2:** Questionnaire 1 (at the time of denture insertion) Reference: [1,6,7]

Sr. No.	Questions	Options	No. of Patients
1.	To what extent do you find the retention of your upper denture satisfactory?	Dissatisfied	
		Neutral	
		Satisfied	
2.	To what extent do you find the retention of your lower denture satisfactory?	Dissatisfied	
		Neutral	

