		Satisfied	
3.	To what extent do you find the chewing ability of your denture satisfactory?	Dissatisfied	
		Neutral	
		Satisfied	
4.	To what extent are you happy with the comfort of your new denture?	Dissatisfied	
		Neutral	
		Satisfied	
5.	To what extent do you find the speech and sound produced by the denture satisfactory?	Dissatisfied	
		Neutral	
		Satisfied	
6.	How satisfied are you with the way your dentures fit and removal?	Dissatisfied	
		Neutral	
		Satisfied	
7.	Does your denture harm the soft tissues in any way?	Yes	
		No	
8.	Do you have any issues with swallowing because of the denture?	Yes	
		No	

**Table 3 TAB3:** Questionnaire 2 (after seven days of denture insertion) Reference: [1,6,7]

Sr. No.	Questions	Options	No. of Patients
1.	To what extent are you satisfied with the adhesive's ability to keep your upper denture in place?	Dissatisfied	
		Neutral	
		Satisfied	
2.	To what extent are you satisfied with the adhesive's ability to keep your lower denture in place?	Dissatisfied	
		Neutral	
		Satisfied	
3.	How was your chewing experience after using this denture adhesive?	Worse	
		No difference	
		Better	
4.	For what duration did the denture adhesive work on your dentures?	≤4 hours	
		4-8 hours	
		8-12 hours	
5.	How does this denture adhesive taste?	Bad	
		Neither good nor bad	
		Good	
6.	How did you find it to remove the adhesive from your dentures?	Difficult	
		Neutral	
		Easy	
7.	How did you find it difficult to clean your denture after using the denture adhesive?	Difficult	
		Neutral	
		Easy	
8.	How difficult was it for you to wipe your oral cavity after using the denture adhesive?	Difficult	
		Neutral	
		Easy	

Sample Size

The sample size is determined using the following formula: n = {(Z 1-α/2 + Z 1-β)2 p1(1-p1) + p2 (1-p2)}/(p1-p2)^2^, where the proportion of outcome from group 1 (p1) = 0.37, the proportion of outcome from group 2 (p2) = 0.22, the level of significance (α) = 0.05, power (1-β) = 0.80, Z alpha value = 1.96, Z beta value = 0.84, and the total sample size = 40. The sample size estimation is done at a 95% confidence interval. Each group consists of 20 samples.

Statistical analysis

The statistical analysis will be done using IBM SPSS Statistics for Windows, Version 23 (Released 2015; IBM Corp., Armonk, New York). Descriptive statistics will be used for the mean distribution of both groups, and an independent sample t-test will be used for intergroup analysis between both groups.

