Age will be given using mean and standard deviation; however, frequency percentage will be used for qualitative characteristics. The independent t-test will be used to compare age between the two groups, and the Pearson chi-square test or Fisher's exact test will be used to compare all qualitative variables at a significant level of p-value ≤0.05 for all variables. The total of each questionnaire's scores will be used to determine the overall satisfaction with the results. Next, choose the percentage of satisfaction for every patient in both groups. The Wilcoxon signed-rank test will be used to compare patient satisfaction before and after the interview.

Ethical considerations

This study has been approved by the Institutional Ethics Committee of Datta Meghe Institute of Higher Education and Research (DMIHER(DU)/IEC/2024/56) dated May 11, 2024. Participant confidentiality will be maintained, and all procedures will adhere to ethical guidelines for research.

Trial registration

The study is registered with the Clinical Trial Registry-India under the CTRI Registration number CTRI/2024/06/068933, registered on June 14, 2024.

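### Questionnaire 1 scores chewing and soft-tissue harm (and, less clearly, swallowing) at denture insertion, before the patient has used the denture, and these answers enter the baseline satisfaction total

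*Protocol article*

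**What the plan says.** The Materials and methods section sets two assessments: "eight during denture insertion without using denture adhesives and eight questions seven days after using denture adhesives". The caption of Table 2 repeats the timing of the first: "Questionnaire 1 (at the time of denture insertion". Once the patient has answered that form, "a clinical examination and application of denture adhesive demonstration will take place, adhering to the guidelines provided by the manufacturer", and seven days of adhesive use follow. No period of wearing the denture without adhesive comes before Questionnaire 1.

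Table 1 admits two kinds of patient: "Patients who are first-time denture wearers" and "Patients who are old complete denture wearers".

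Three items of Questionnaire 1 (Table 2) concern the denture in use. Item 3 asks for satisfaction with chewing. Item 7 asks "Does your denture harm the soft tissues in any way". Item 8 asks "Do you have any issues with swallowing because of the denture". Item 3 has three levels; items 7 and 8 are yes/no. None has a not-applicable option. Item 4, on comfort, describes the denture as new.

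Under Statistical analysis, "The total of each questionnaire's scores will be used to determine the overall satisfaction with the results". A percentage of satisfaction per patient follows, and a Wilcoxon signed-rank test compares satisfaction before and after. No item is exempted from the total.

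**The concern.** Two of these items, and perhaps a third, are scored before the experience they ask about. At insertion, a patient with a new denture has not eaten a meal with it, so the chewing answer is a guess or an expectation. There has been no time for a sore to form, so No to tissue harm is close to automatic. Swallowing is less clear-cut, because a first impression is possible in the chair.

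The result at stake is the before-after change. If part of the baseline is set by when the form is handed out, the change from baseline partly reflects that timing and not the adhesive.

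**Working it through.** The plan gives no figure on this point to reproduce. The check sets the stated sequence against the items and then works out how much of the score is involved.

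**Sequence against content** (timing from Materials and methods; items from Tables 2 and 3)

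| Questionnaire 1 item | Can it be judged at insertion of a new denture? | Counterpart in Questionnaire 2 |
|---|---|---|
| 1, 2 Upper and lower retention | Yes, in the chair | Items 1, 2 |
| 3 Chewing | No, needs eating | Item 3, worded as worse / no difference / better |
| 4 Comfort | First impression only | None |
| 5 Speech | Yes, in the chair | None |
| 6 Fitting and removal | Yes, in the chair | None (items 6 and 7 there concern removing adhesive and cleaning) |
| 7 Soft-tissue harm | No, needs wearing time | None |
| 8 Swallowing | Partly | None |

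That the denture has not been used is an inference. It follows from the insertion timing, the reference to a new denture in item 4, and the adhesive demonstration coming straight after the form.

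**Share of the score.** The article does not state item scores, so two schemes are assumed, with No counted as the favourable answer on items 7 and 8.

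Scheme A, three-level items 0-2 and yes/no items 0-1:
- Range of the total: 6 × 2 + 2 × 1 = 14
- Items 3 and 7: (2 + 1)/14 = 3/14 = 21.4%
- Items 3, 7 and 8: (2 + 1 + 1)/14 = 4/14 = 28.6%

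Scheme B, all items 0-2:
- Range of the total: 8 × 2 = 16
- Items 3 and 7: 4/16 = 25.0%
- Items 3, 7 and 8: 6/16 = 37.5%

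**Most that an automatic No could add to the percentage of satisfaction.** Item 7 alone: 1/14 = 7.1 percentage points (A) or 2/16 = 12.5 (B). Items 7 and 8 together: 2/14 = 14.3 (A) or 4/16 = 25.0 (B). These are ceilings. They would be reached only if the answer after some use would have been Yes.

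**Direction.** A higher baseline makes the after-minus-before difference smaller. The artefact from items 7 and 8 therefore works against showing a gain with adhesive. The guess on item 3 has no known direction; it adds noise.

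**The case against.** **The main comparison is untouched.** The stated aim is to compare two adhesives in randomised groups. Both groups answer the same form at the same moment, so the artefact is common to both and does not bias the comparison at day 7 in expectation. This stands. The point concerns the before-after result only.

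**New and old wearers.** A reader might infer that old wearers answer these items from experience and first-time wearers do not, so that the baseline means different things in the two. The article does not support this. It never says that old wearers rate a denture already in use, and item 4 asks every patient about a new one. An old wearer being fitted with a new denture has no more experience of that denture than a first-time wearer.

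**The percentages.** A reader might take 21% or 29% as the size of the bias. They are shares of an assumed score range. The article holds no data from which a bias could be estimated.

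**The form is taken from cited sources.** The article calls it a standard questionnaire, and dropping items departs from it. That is a real cost. However, items 7 and 8 have no counterpart in Questionnaire 2, so they add nothing to a like-for-like change.

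**Chewing is one of only three topics shared by both forms.** Dropping it from the baseline does thin the match. But item 3 of Questionnaire 2 already asks whether chewing became worse or better. That answer is itself a change, and subtracting a baseline rating from it would not give a meaningful difference.

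**Conclusion.** The point holds, as a minor one. Questionnaire 1 scores chewing and soft-tissue harm before a patient with a new denture can judge them from use, and swallowing with less basis than after wear. These answers go into the baseline total. The expected effect is noise from item 3 and a raised baseline from item 7, possibly item 8, which shrinks the apparent before-after gain.

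The items involved make up 21% (items 3 and 7) to 29% (items 3, 7 and 8) of the score range under 0-2/0-1 scoring, and 25% to 38% if every item is scored 0-2.

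This rests on four assumptions: the item scores above; No being scored as favourable; no use of the denture before the form is completed; and the Wilcoxon test comparing the Questionnaire 1 and Questionnaire 2 results, which is its natural reading. It does not show bias between the two adhesive groups, or a difference between first-time and old wearers.

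**What to change.** Change the scoring text under Statistical analysis as follows:

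- Leave items 7 and 8 out of the Questionnaire 1 total and the percentage of satisfaction, and report them descriptively.
- Leave item 3 out of the insertion-time total as well. Report the change in chewing from item 3 of Questionnaire 2, which asks for it directly.
- Keep item 4 (comfort) and label it a first impression. The insertion-time total then consists of items 1, 2, 4, 5 and 6, with a range of 5 × 2 = 10 points under 0-2 scoring.
- Base the before-after Wilcoxon comparison on upper and lower retention, items 1 and 2 of both forms, and not on the two unlike totals.

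The cost is a shorter baseline score that departs from the cited questionnaire form, and a before-after comparison confined to retention. No visit, patient or question is added. The change does not separate a week of getting used to the denture from the effect of the adhesive; the before-after result should be worded with that limit.

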Denture adhesives are categorized based on their forms, such as powder, tapes, gels, and paste. Denture adhesive enhances retention, lessens denture soreness, avoids strangling the mucosal blood supply, and lessens the need for adjustments even when the denture fits [4]. Additionally, there have been reports of improvements in biting force and chewing efficiency, which lead to a wider dispersion of occlusal forces over the tissues supporting the denture and a decrease in local pressure. The lubricating and cushioning properties of adhesives lessen friction and discomfort in the mucosa. Denture adhesives can be very beneficial for patients with muscle control deficiencies caused by hormonal or neurotransmitter abnormalities [5]. This study aims to evaluate and compare two different types of commercially available herbal denture adhesives with regard to patient satisfaction with denture retention.

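### The retention items rate the denture at insertion but the adhesive at day 7, so the planned before/after comparison of satisfaction has no matched item to rest on

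*Protocol article*

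**What the plan says.** The last paragraph of the Introduction gives the aim: to "evaluate and compare two different types of commercially available herbal denture adhesives with regard to patient satisfaction with denture retention".

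Materials and methods describes two questionnaires: "eight during denture insertion without using denture adhesives and eight questions seven days after using denture adhesives". Both are printed in full.

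- Table 2 (at insertion), items 1 and 2: "To what extent do you find the retention of your upper denture satisfactory" and "To what extent do you find the retention of your lower denture satisfactory". The options are Dissatisfied, Neutral and Satisfied.
- Table 3 (day 7), items 1 and 2: "To what extent are you satisfied with the adhesive's ability to keep your upper denture in place" and "To what extent are you satisfied with the adhesive's ability to keep your lower denture in place". The options are the same three.

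The Statistical analysis section builds the outcome from sums: "The total of each questionnaire's scores will be used to determine the overall satisfaction with the results". It compares satisfaction before and after with a Wilcoxon signed-rank test. Between groups it uses an independent t-test, and chi-square or Fisher's exact test for qualitative variables.

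**The concern.** A paired test is informative only if the same quantity is measured on both occasions. Items 1 and 2 look like a proper pair because the topic and options agree, and they are the only questions that address retention directly. The object of the rating changes, however. At insertion the patient judges how well the denture holds. A week later the patient judges how well a product does its job.

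The article's own prose suggests that a like-for-like comparison was intended. The Abstract describes one questionnaire, covering chewing, retention and stability, completed at both times. The Methods text says that at day 7 patients rate properties of the denture with the adhesive in use. Table 3 items 1 and 2 do not ask that.

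At stake is whether the trial can say that satisfaction with retention changed from insertion to day 7.

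**Working it through.** There is no figure in the plan to reproduce here. The check is an item-by-item comparison of Tables 2 and 3, followed by a decomposition of the change score.

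**Step 1. Match the items.**

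| Item | Table 2 (insertion) | Table 3 (day 7) | Match |
|---|---|---|---|
| 1 | Upper denture: retention | Upper denture: adhesive's holding ability | Same topic and options, different object |
| 2 | Lower denture: retention | Lower denture: adhesive's holding ability | Same topic and options, different object |
| 3 | Chewing, rated as a level | Chewing, rated as worse / no difference / better | Same topic, but a level becomes a change |
| 4 | Comfort | Hours of adhesive action | None |
| 5 | Speech | Taste | None |
| 6 | Fit and removal of the denture | Removal of the adhesive | None |
| 7 | Tissue harm (yes/no) | Cleaning the denture | None |
| 8 | Swallowing (yes/no) | Cleaning the mouth | None |

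Count: 2 + 1 + 5 = 8 pairs. Two share topic and options, one shares topic only, and five share neither question nor purpose. The number asked identically at both times is 0 of 8.

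**Step 2. See what a change on items 1 and 2 contains.** Let R0 be satisfaction with retention at insertion (asked), R7 the same at day 7 (not asked), and A7 satisfaction with the adhesive's holding ability at day 7 (asked). Then

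A7 − R0 = (R7 − R0) + (A7 − R7).

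The first bracket is the change of interest. The second arises only from changing the object rated. Since R7 is never collected, the two cannot be separated.

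**Step 3. Check whether the second term has a known sign.** The article gives no item coding, so assume Dissatisfied = 0, Neutral = 1, Satisfied = 2. Three possible patients (illustrations, not estimates):

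| Patient | R0 | R7 | A7 | True change R7 − R0 | Wording term A7 − R7 | Recorded change A7 − R0 |
|---|---|---|---|---|---|---|
| Denture already held well; adhesive seen as adding little | 2 | 2 | 1 | 0 | −1 | −1 |
| Denture still loose; patient credits the product | 0 | 0 | 2 | 0 | +2 | +2 |
| Denture loose, then held; patient credits the product | 0 | 2 | 2 | +2 | 0 | +2 |

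The wording term can be negative, positive or zero. Nothing in the article says how often each pattern occurs.

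**Step 4. Check the comparison between groups.** Both arms answer the same A7 items, so the difference in A7 between arms is well defined. It equals the difference in R7 only if the average of A7 − R7 is the same in both arms. Otherwise it is a valid comparison of product satisfaction, which is close to the aim but not expressed in the baseline terms.

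**The case against.** The strongest reply is that the aim is a comparison between two adhesives, which needs no matched baseline wording. Holding a denture in place is retention in lay language, and in an adhesive trial, satisfaction with that is near the target. Some patients may answer both wordings alike. Both tables also cite source questionnaires that are not at hand, so the paired wording may be established practice. Much of this stands. The day-7 comparison between groups is not undermined, and it would be wrong to say that the day-7 form ignores retention.

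Four stronger readings are tempting, but the document does not support them.

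- **That the endpoint is formally defined by these items.** The article gives no such definition and builds satisfaction from questionnaire totals. Items 1 and 2 are simply the only direct questions on retention.
- **That the wording makes patients look worse.** The day-7 items ask about satisfaction with holding the denture, not whether the adhesive added anything. A patient whose denture stays put may answer Satisfied. The direction is open.
- **That the upper denture is most at risk.** The Discussion cites a 30-patient study with no significant gain in maxillary retention. That concerns retention, not how patients respond to a reworded item.
- **That the loss can be expressed as a shift in a p-value.** This would need response rates that the article does not give, and an item-level paired test that it does not state.

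A further objection is that the larger defect lies in the totals: five of the eight pairs are unrelated, so rewording two items leaves a before/after test on totals as unsound as before. That is correct. It is why the fix must also change what the before/after retention comparison is based on.

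**Conclusion.** The point holds for the before/after comparison. The two retention items, which are the only pairs with the same topic and options, change object from denture to adhesive. None of the eight questions is asked identically at both visits. A recorded change in satisfaction with retention cannot be separated from the effect of asking about something else, and its direction and size cannot be determined from the document.

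The comparison between groups at day 7 remains usable, but should be described as satisfaction with the adhesive's hold.

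This conclusion rests on the printed wording of Tables 2 and 3 and on the planned paired test, with no numerical assumption. A statistical analysis plan could not repair it, since no analysis recovers an answer that was not collected. It is worth correcting because the change is small and bears on the stated aim, but it does not invalidate the trial.

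**What to change.** 1. At day 7, ask Table 2 items 1 and 2 again, each followed by *while using the adhesive*: "To what extent do you find the retention of your upper denture satisfactory" and "To what extent do you find the retention of your lower denture satisfactory", with the same three options.
2. Base the before/after retention comparison (Wilcoxon signed-rank) on these two matched items, not on the unmatched questionnaire totals.
3. Keep the present Table 3 items 1 and 2 as separate product ratings, compared between groups and left out of the before/after retention measure.

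If the forms are already in use, add the two items rather than replacing the existing ones. Patients who answered only the old form then have no matched day-7 value and should be reported as such.

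The cost is two reworded or added questions and a small departure from the source questionnaires. No extra visit or patient is needed. Matched wording makes the change interpretable as a change in satisfaction with retention. It does not by itself attribute that change to the adhesive, because both groups use one.

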## Results

The current study's findings will indicate that the application of herbal denture adhesive combined with essential oil will considerably improve the overall comfort of using the complete denture. It will reduce the bacterial growth and chances of mouth sores due to dentures. The expected results of the study indicate that the utilization of herbal denture adhesive combined with essential oil will increase the stability and retention of the dentures and the effectiveness of their retention over time.

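### Table 3 item 4 cannot show that the adhesive was still holding when the denture was taken out, so for removals before 8 h the answer can reflect wearing time rather than duration of hold

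*Protocol article*

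**What the plan says.** In Materials and methods, Table 3 item 4 asks "For what duration did the denture adhesive work on your dentures". The three options, printed in full, are ≤4, 4-8 and 8-12 hours. The form is filled in once, as part of "eight questions seven days after using denture adhesives".

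On use during the week, the article says: "The patients will be provided with an explanation of the cleaning routine and the administration of denture adhesive for the next seven days". It gives no daily wearing time and no times of removal, and neither Table 2 nor Table 3 asks for them.

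On analysis, the Statistical analysis section says that "the Pearson chi-square test or Fisher's exact test will be used to compare all qualitative variables", and also: "The total of each questionnaire's scores will be used to determine the overall satisfaction with the results". On size: "Each group consists of 20 samples".

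The Results section expects that the adhesive with essential oil "will increase the stability and retention of the dentures and the effectiveness of their retention over time". Item 4 is the only question in either form about how long the hold lasts. It is not named as a primary outcome.

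**The concern.** Duration of hold can be observed only while the denture is worn. If the denture comes out while the adhesive still holds, the patient knows only that the hold lasted at least that long. In statistical terms the answer is right-censored, and the form has no mark for this. Two different facts, loosening at 6 h and removal at 6 h with the hold intact, end in the same box.

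The planned comparison takes each tick at face value. If the two groups have similar wearing habits, early removal cuts short the longer-holding product more often, and a real difference in "the effectiveness of their retention over time" may look smaller than it is. The information is lost when the form is filled in, so a later analysis plan cannot restore it. The same answers may also enter the questionnaire total.

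This is separate from the limits of the bands. Non-overlapping bands and an open top band would not help a patient who removes the denture at 6 h.

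**Working it through.** **Inputs from the article.** Three bands with boundaries at 4 h and 8 h, and 20 patients per group. The article states no figure for item 4, so there is none to reproduce. Hold times and wearing times are not given, and everything about them below is an assumption.

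**Which answers are affected.** Let T be the time the adhesive would hold and R the time of removal. What the patient can observe is min(T, R). The band is wrong for T only if R falls before a boundary (4 h or 8 h) that T would have passed. A removal after 8 h already falls in the top band and costs nothing at these boundaries.

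**Formula.** If removal is unrelated to hold, P(recorded > 8 h) = P(T > 8) × P(R > 8). With the same wear in both groups, the recorded difference is the true difference multiplied by P(R > 8).

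**Model 1.** T is Weibull with shape 2, with median 6 h in group A and 9 h in group B. A fraction f of patients remove the denture at 4-8 h, and the others not before the hold is lost.

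- A: P(T > 8) = 2^−(8/6)² = 0.29
- B: P(T > 8) = 2^−(8/9)² = 0.58
- True difference: 29 points

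| f | A beyond 8 h | B beyond 8 h | Recorded difference |
|---|---|---|---|
| 0 | 29% | 58% | 29 points |
| 25% | 22% | 43% | 21 points |
| 50% | 15% | 29% | 14 points |
| 75% | 7% | 14% | 7 points |

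The standard error of the undiluted difference at 20 per group is √(0.29 × 0.71/20 + 0.58 × 0.42/20) = 0.15. The losses of about 7, 14 and 22 points are therefore about 0.5, 1.0 and 1.4 standard errors. Measured against the smaller standard errors of the diluted differences (0.144, 0.128 and 0.098), they are 0.5, 1.1 and 2.2. With medians of 7 h and 9 h, the figures on that second scale are 0.3, 0.65 and 1.3.

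**Model 2.** T is normal with mean 7 h (A) and 10 h (B), SD 2.5 h. Wearing time is normal with SD 2 h and the same mean in both groups. Then P(T > 8) is 0.345 and 0.788, a true difference of 44 points.

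| Mean wear | P(R > 8) | Recorded difference | Power, 20 per group |
|---|---|---|---|
| no early removal | 1 | 44 points | 0.87 |
| 6 h | 0.159 | 7 points | 0.15 |
| 8 h | 0.500 | 22 points | 0.45 |
| 10 h | 0.841 | 37 points | 0.76 |
| 12 h | 0.977 | 43 points | 0.86 |
| 14 h | 0.999 | 44 points | 0.87 |

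The power column comes from simulation of a two-sided t-test on the item scored 0/1/2. It is a guide to scale and not the power of the article's chi-square or Fisher test. Mean hold times of 6 h against 8 h, or 9 h against 12 h, show the same pattern: a true 29 points becomes about 5, 15, 24 and 28 points at mean wear of 6, 8, 10 and 12 h.

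**Unequal wear.** Give both groups the same mean hold of 9 h (SD 2.5 h), so P(T > 8) = 0.655. With mean wear of 8 h in A and 12 h in B, the recorded shares are 0.655 × 0.500 = 0.33 and 0.655 × 0.977 = 0.64. That is a false difference of 31 points.

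**The case against.** The strongest reply is that the premise is about behaviour that the article does not describe. A reader might infer from the cleaning routine that dentures come out at times unrelated to loss of hold. The text says only that the routine and the application will be explained. It gives no frequency or timing, and one removal at the end of the day would fit it. If that is the usual pattern, most removals fall after 8 h and item 4 loses almost nothing. This stands.

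A reader might also say that the item records a failure that never happened. It does not: it asks how long the adhesive worked, and a patient who saw it hold for 6 h before removal answers truthfully with 4-8 hours. The plan nowhere calls item 4 a failure time. What remains is that the answer is then a lower limit on the hold, and nothing on the form says so.

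The size is open to challenge too. In Model 1 the result is (1 − f) times 29 points by construction, and f has no source. Both models give each patient one hold time and one removal time, whereas the form asks for one recollection after a week. A patient may answer from the longest day or from a general impression. The figures therefore show what could happen and do not predict it.

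Finally, the article's aim is satisfaction with retention, which items 1 and 2 ask directly. Item 4 is one of eight questions. That limits the importance of the point but does not remove the ambiguity.

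**Conclusion.** The point holds in a limited form. The printed options do not separate an adhesive still holding at removal from one that gave way, and the analysis cannot recover the distinction. For patients who remove a firmly held denture before 8 h, the answer can reflect wearing time.

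The stronger reading, that a real group difference will shrink, is not supported, because it depends on wearing times that the article does not give:

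- If many patients remove the denture before 8 h and wear is similar in both groups, a real difference may be attenuated. Under the assumed medians of 6 h and 9 h, 29 points becomes 21, 14 or 7 for early removal in 25%, 50% or 75% of patients.
- If wear is mostly beyond 8-12 h, the loss is negligible: about 1 point at a mean wear of 12 h in the second model.
- If wear differs by group, the bias can go either way, including a difference where none exists.

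These figures assume that removal is unrelated to hold. The item is secondary, and the point is a low-cost improvement rather than a flaw that threatens the trial.

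**What to change.** Keep item 4 and its bands, and add one tick beneath it: *Had it become loose by then? Yes / No, still holding when I removed it.*

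Report by group how often the second answer was ticked. Do not read those answers as loss of hold. For example, add a sensitivity comparison that treats them as held for at least the ticked band. Leave the scoring of the satisfaction total unchanged. A model for censored data is optional: with one recalled item and 20 patients per group it is not needed, and it would rest on removal being unrelated to hold, which is doubtful if loosening or discomfort prompts removal.

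The cost is one extra tick box and slightly more analysis of one secondary item. No visit, staff or patients are added. The tick must be on the form before Questionnaire 2 is given out, because the information cannot be recovered afterwards.
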